### Development of asthma risk appraisal tool

We will convert the updated PIAMA Risk Score to a computer-assisted tool, the so called ‘Asthma Risk Appraisal Tool’. The best cut-off scores of the Asthma Risk Appraisal Tool will be studied within the validation study. In an expert meeting we will discuss which decisions will follow the cut-offs: referral to general practitioner (=indirect referral to pediatrician)/ asthma nurse, extra consultation moment at well-child care, personal advise/counselling. The aim is to create an easy applicable (computer-assisted) tool for use of the PIAMA Risk Score in well-child care. A previous study developed a similar risk assessment tool to early detect children with global developmental disabilities in well-child care
[18]. A computer-assisted risk assessment tool heightens the uniformity of practice.

### Pilot testing

After development of the Asthma Risk Appraisal Tool, the tool will be tested in a pilot study within well-child care. The pilot test will be conducted in the Rotterdam-Rijnmond area that contains both rural and metropolitan and ethnically diverse sub-regions. The implementation will involve 3 varied well-child care teams (including one or more well-child care physicians, nurses and medical assistants per team that provide services to a certain group of preschool children in a distinct geographical region). It is aimed to pilot the Asthma Risk Appraisal Tool to 100 children/families. So, a total of 300 children/families are aimed to be included in the pilot study.

When children present with asthma symptoms, the Asthma Risk Appraisal Tool will be applied. In the pilot study we will assess how many preschool children were detected as high-risk of developing asthma at the ages of 6 and 9 years by the Asthma Risk Appraisal Tool. We will evaluate which decisions cq. actions were taken by physicians/nurses after the use of the Asthma Risk Appraisal Tool (and how many times). Evaluation of the effectivity of implementation of the Asthma Risk Appraisal Tool in well-child care practice is outside the framework of this study.

### Sample size

At least 100 patients with the outcome and 100 without the outcome are needed for reliable external validation of a prediction model
[19].

Sample size at the age of 6 years: Assuming a prevalence of asthma of 5% at the age of 6 years (and it is known that 3967 children have ever had asthma symptoms at the age of 4 years) the Generation R study will have approximately 198 children aged 6 years
[19]. This implies that our effective sample size at the age of 6 years is sufficiently large for the primary aim of this study.

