## Methods and design

### Design and setting

Our study will be embedded in Generation R, a prospective population-based, multi-ethnic cohort study. In total, consent for postnatal follow-up was obtained from 7893 children, born between April 2002 and January 2006
[13]. Questionnaires for parental completion, partly based on the International Study of Asthma and Allergies in Childhood (ISAAC) core questionnaires
[14], were sent to the parents during pregnancy and when the children were aged 1, 2, 3, 4 and 6 years (N=7893)
[15]. Response rates for these questionnaires were 71%, 76%, 72%, 73% and 68% respectively. Data collection at child’s age of 9 years is currently ongoing. In this study, children will be included if at least one positive response was given to the following questions in the annual questionnaires at age 1 to 4 years: “Has your child had wheezing in the last 12 months?” and “Has your child had cough during the night, when he/she did not have a cold or a chest infection, in the last 12 months?” The present study was conducted in accordance with the guidelines proposed in the Declaration of Helsinki, and is approved by the Medical Ethical Committee of the Erasmus Medical Centre (MEC 217.595/2002/202). Written consent was obtained from all participating parents.

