### Asthma outcomes

The outcome that is predicted with the PIAMA Risk Score is asthma at school age. In the development study (PIAMA) the following 3 items were used for the case definition of asthma: (1) at least 1 episode of wheezing in the last 12 months; (2) inhaled steroids prescribed by a medical doctor in the last 12 months; and (3) a doctor’s diagnosis of asthma (a parental report of a doctor’s diagnosis of asthma at any time and a parental report of asthma in the last 12 months). In the analyses children were only considered positive for asthma if they had 1 or more positive items at age 7 years and 1 or more positive items at age 8 years
[7].

Within the validation data (Generation R), we aim to use the same asthma definition as used in PIAMA and we aim to select only children with ‘active asthma’ or clinically relevant chronic asthma symptoms. First, we will define asthma at the age of 6 years in the children who have ever had reported asthma symptoms before the age of 4 years. Additionally, the analyses will be repeated in children at age 9 years. At age 9 years spirometry will be performed in children at the research center. Spirometry is used to improve the accuracy of an asthma diagnoses and will be enable us to compare asthma outcomes based on parental reports to asthma outcomes based on spirometry.

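### The 198 expected asthma cases at age 6 make no allowance for age-6 non-response; at the cohort's 68% response the figure is about 135, still above the plan's minimum of 100

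*Protocol article*

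**What the plan says.** The Sample size section of the protocol article sets its criterion first: "At least 100 patients with the outcome and 100 without the outcome are needed for reliable external validation of a prediction model". It then gives two inputs. The first is a prevalence: "Assuming a prevalence of asthma of 5% at the age of 6 years". The second is the number of children with symptoms: "it is known that 3967 children have ever had asthma symptoms at the age of 4 years". The section concludes that "the Generation R study will have approximately 198 children aged 6 years". Read literally, that sentence counts children aged 6. Only a count of children with asthma at age 6 fits the two inputs. On this basis the section judges the effective sample size at age 6 to be adequate for the primary aim.

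The Design and setting section says that the questionnaires "were sent to the parents during pregnancy and when the children were aged 1, 2, 3, 4 and 6 years (N=7893") and adds: "Response rates for these questionnaires were 71%, 76%, 72%, 73% and 68% respectively". The last rate belongs to the last wave, age 6. The same section defines entry, with ages in years: "children will be included if at least one positive response was given to the following questions in the annual questionnaires at age 1 to 4". The Asthma outcomes section, again with ages in years, says "we will define asthma at the age of 6 years in the children who have ever had reported asthma symptoms before the age of 4". It aims to use the PIAMA items (wheeze, prescribed inhaled steroids, reported doctor's diagnosis) and mentions spirometry only for age 9.

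**The concern.** The 3967 is a count of children with symptoms in the preschool years. The effective sample for the age-6 validation is the part of that group with an age-6 outcome. For age 6 the article names no source for the outcome other than parental report, so a child whose age-6 questionnaire did not come back has no stated outcome. The response rate was already known and is printed in the same article, yet the calculation does not use it. Nothing says that the 3967 is restricted to children with age-6 data.

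The 198 is the only number offered in support of adequacy. If it is too high, the margin over the plan's own minimum is smaller than it appears. The C-index will be less precise, and the validations planned by age, ethnicity and socioeconomic status will have fewer events.

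**Working it through.** **Inputs**

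- Children with preschool symptoms: 3967 (Sample size)
- Assumed prevalence at age 6: 5% (Sample size)
- Minimum: 100 with and 100 without the outcome (Sample size)
- Response at age 6: 68% of 7893 (Design and setting)
- AUC in the development study: 0.72 (Background)

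**Step 1: reproduce the plan's figure.** Events = N × prevalence = 3967 × 0.05 = 198.35, about 198. It reproduces without any response factor, so it implies 100% follow-up to age 6.

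**Step 2: apply the cohort response rate.** Events = N × response × prevalence.

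- 3967 × 0.68 = 2697.6, about 2,698 children with an outcome
- 2697.6 × 0.05 = 134.9, about 135 cases
- 2697.6 × 0.95 = 2562.7, about 2,563 non-cases

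**Step 3: vary the response.** The 68% refers to all 7893 children, not to the 3967. The rates between 68% and 100% below are assumptions.

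| Age-6 response among the 3967 | Children with outcome | Cases at 5% |
|---|---|---|
| 68% (cohort rate) | 2,698 | 135 |
| 76% | 3,015 | 151 |
| 80% | 3,174 | 159 |
| 85% | 3,372 | 169 |
| 90% | 3,570 | 179 |
| 100% (implied by the plan) | 3,967 | 198 |

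**Step 4: what the documents alone allow.** Age-6 responders: 0.68 × 7893 = 5367. Children outside the 3967: 7893 − 3967 = 3926. If all 3926 responded, 5367 − 3926 = 1441 responders would be left among the 3967. At the other extreme all 3967 responded. At 5% prevalence this gives 1441 × 0.05 = 72 to 198 cases. The lower end would need symptomatic children to respond at only 1441 / 3967 = 36%.

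**Step 5: margin over the minimum of 100.**

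- At 100% response: 198 − 100 = 98. At 68%: 135 − 100 = 35.
- Prevalence needed for 100 events: 100 / 3967 = 2.5% at full response; 100 / 2697.6 = 3.7% at 68%.
- Response needed for 100 events at 5% prevalence: 100 / 198.35 = 50.4%.

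**Step 6: precision of the C-index at 0.72 (Hanley–McNeil).** SE² = [A(1−A) + (n₁−1)(Q₁−A²) + (n₀−1)(Q₂−A²)] / (n₁n₀), where A = 0.72, Q₁ = A/(2−A) = 0.5625, Q₂ = 2A²/(1+A) = 0.6028 and A² = 0.5184.

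- 198 cases, 3,769 non-cases: SE = 0.0209; half-width 1.96 × 0.0209 = 0.041
- 135 cases, 2,563 non-cases: SE = 0.0253; half-width 1.96 × 0.0253 = 0.050

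**Step 7: subgroups.** To reach 100 events, a subgroup must hold 100 / 198.35 = 50% of the cases under the plan's figure and 100 / 134.9 = 74% at 68% response. A subgroup holding half of the cases has about 99 or about 67.

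**The case against.** The strongest objection is that 135 is not a figure the article itself establishes. The 68% is a whole-cohort rate. Each of the 3967 entered through at least one returned questionnaire at ages 1 to 4, so families that never respond are excluded, and age-6 response in this group may be higher than 68%. This stands. For that reason 135 is given only as the value at the cohort rate, with a range beside it. It does not rescue 198, which is reached only at 100% response.

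A second objection is that the 5% is itself an assumption. At 68% response a prevalence of 198.35 / 2697.6 = 7.35% would bring the count back to 198. This also stands: the true number of events is not known from the article. What can be said is that, at the plan's own 5%, the calculation leaves out a loss that the plan reports.

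A third objection is that nothing in the design changes, since 135 still exceeds 100 and the cohort is already assembled. That is correct and limits the weight of the point.

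A reader might also go further and add the 24% to 29% non-response at the preschool waves as a second loss that takes the validation below 100 events. The documents do not support this. Those are whole-cohort rates, whereas every included child returned at least one preschool questionnaire. Wheezing frequency, infections and eczema come from those same questionnaires, and the remaining available predictors from medical records or pregnancy questionnaires. No rate of missing items is given, no complete-case analysis is specified, and the handling of missing data may be set out in an analysis plan that is not shown.

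**Conclusion.** The point holds in a limited form. As written, 198 counts cases among all children with preschool symptoms, not among those with an age-6 outcome, and it makes no allowance for the non-response that the article reports. With 5% prevalence and response at the cohort rate, the expected number is about 135, which is 32% below the stated figure (1 − 134.9 / 198.35). With an assumed 76% to 90% response it is about 151 to 179.

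Two stronger conclusions might be inferred and are not supported. One is that the sample is too small: at 68% response the minimum of 100 events and 100 non-events is met, and at 5% prevalence the count drops below 100 only if age-6 response among the 3967 is under 50.4%. The other is that age-9 events are capped at 135 unless response improves: the article gives no age-9 prevalence and adds a spirometry-based outcome at that age, so no such ceiling follows.

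What changes is the margin (about 35 events instead of 98), the precision of the C-index, and the number of events available to each subgroup validation.

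**What to change.** In the Sample size section, replace 198 with the actual number of the 3967 who have age-6 outcome data and the number of events that follows. Response at age 6 is already reported, so the count should be obtainable. If it is not, state that 3967 × 68% gives about 2,698 children and about 135 cases at 5% prevalence, name the cohort-rate assumption, and show the range (about 151 to 179 cases at 76% to 90% response). If the 3967 already counts only children with age-6 data, one sentence saying so settles the matter. The wording should also say that the number refers to children with asthma.

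The cost is one revised paragraph. The stated figure becomes less favourable unless the 3967 is already restricted, and the judgement of adequacy for the primary aim can stay if the count with outcome data supports it.

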## Discussion

We present the rationale and design of a study to externally validate and update the PIAMA Risk Score and to develop and test an application of the PIAMA Risk Score to predict asthma at school age in (specific subgroups of) preschool children with asthma symptoms. This Asthma Risk Appraisal Tool might be used in well-child care as an Asthma Risk Appraisal Tool in preschool children already detected with asthma symptoms.

Several studies previously developed a prediction model to predict asthma
[5-12]. It is complicated to compare these studies, because definitions and age of asthma differs and it is unknown which definition of asthma truly identifies the disease. Many studies used information up to a fixed age irrespective of the age of symptom onset
[6,8,10,11]. Some of the prediction models included blood tests
[6,11,12]. Prediction models including blood tests are not feasible in well-child care, given the (very) low acceptance of drawing blood in the setting of prevention by parents and children, the lack of funding for laboratory tests in preventive healthcare, and because laboratory results should be awaited. Therefore, the PIAMA Risk Score - including only easy obtainable parameters - is preferred above prediction models including blood tests. The PIAMA Risk Score has been compared to the asthma predictive index developed by Castro-Rodriquez et al.
[6] and showed a better predictive ability, and also performed better than a doctors diagnosis of asthma at the same age
[7].

This study benefits from a longitudinal design, which enables us to collect repeated measurements of predictors at preschool age. In this way we can identify the age at onset of first symptoms, unlike some earlier studies who predict asthma at fixed ages
[6,8,10,11]. The ages at which asthma symptoms appear most frequently is the time that children will regularly visit well-child care and when prediction of asthma becomes relevant. Furthermore, there will be little differences in design and analysis between the development and the validation study. It is our intention to develop an Asthma Risk Appraisal Tool integrated in well-child care at preschool age in such a way that it has maximal opportunity for future wide-spread implementation, once proved useful.

There are several reasons why early detection followed by risk assessment of asthma is important: early detection of preschool children at high risk of developing asthma at school age will contribute to adequate and early management, resulting in fewer asthma symptoms, while improving child’s quality of life
[4,20]. Furthermore, for parents of preschool children it is important to know the risk of developing asthma at school age, and the options for treatment or intervention to reduce or prevent progression of asthma symptoms.

Risk assessment is important because in well-child care (in the Netherlands) task reallocation is ongoing: an approach where children and families with the highest risks on health and psychosocial problems receive higher levels of preventive care and monitoring. Those with low risk of health and psychosocial problems should be offered care at a basic level in terms of frequency, content and type of professional. The background of this approach is often budgetary pressure. In most cases nowadays, risk selection is carried out by a trained healthcare assistant based on predefined factors at preschool age (e.g. socioeconomic status, single parenting, child health, paternal psychopathology). Although child’s health at preschool age is one of the factors which is included in the approach of risk selection at school age, no specific attention is given to preschool child’s asthma symptoms or preschool child’s risk of developing asthma at school age. To prevent inadequate treatment of childhood asthma and to prevent that children with an increased risk of asthma are lost to follow up by primary and secondary healthcare, it is important to assess the risk of developing asthma at school age when preschool children present with asthma symptoms at well-child care.

The aim of improved risk assessment of asthma is to achieve optimal asthma management without delay in preschool children with symptoms suggestive of asthma who are at high risk of developing asthma. In turn, the aim of optimal asthma management is to reduce and prevent the burden of asthma in the future and to improve the child’s quality of life. However, this topic is outside the framework of this study. After pilot testing and implementation, a randomised controlled trial is a possible next step to evaluate the effectivity of the use of an Asthma Risk Appraisal Tool in well-child care to support professionals in risk assessment of asthma, when preschool children present with asthma symptoms.

## Conclusion

This study will increase knowledge about the external validity of the PIAMA risk score and might improve risk assessment of developing asthma at school age in (specific subgroups of) preschool children, who present with asthma symptoms at well-child care.

## Abbreviations

C-index: Concordance-index; ISAAC: International study of asthma and allergies in childhood; ORs: Odds ratios; PIAMA: Prevention and incidence of asthma and mite allergy.
